## Abstract

**Background:**

Preterm infants represent up to 10% of births worldwide and have an increased risk of adverse metabolic outcomes in later life. Early life exposures are key factors in determining later health but current lifestyle factors such as diet and physical activity are also extremely important and provide an opportunity for targeted intervention.

**Methods/Design:**

This current study, GROWMORE, is the fourth phase of the Newcastle Preterm Birth Growth Study (PTBGS), which was formed from two randomised controlled trials of nutrition in early life in preterm (24–34 weeks gestation) and low birthweight infants. 247 infants were recruited prior to hospital discharge. Infant follow-up included detailed measures of growth, nutritional intake, morbidities and body composition (Dual X Ray Absorptiometry, DXA) along with demographic data until 2 years corrected age. Developmental assessment was performed at 18 months corrected age, and cognitive assessment at 9–10 years of age. Growth, body composition (DXA), blood pressure and metabolic function (insulin resistance and lipid profile) were assessed at 9–13 years of age, and samples obtained for epigenetic analysis. In GROWMORE, we will follow up a representative cohort using established techniques and novel metabolic biomarkers and correlate these with current lifestyle factors including physical activity and dietary intake. We will assess auxology, body composition (BODPOD™), insulin resistance, daily activity levels using Actigraph™ software and use ^31^P and ^1^H magnetic resonance spectroscopy to assess mitochondrial function and intra-hepatic lipid content.

**Discussion:**

The Newcastle PTBGS is a unique cohort of children born preterm in the late 1990’s. The major strengths are the high level of detail of early nutritional and growth exposures, and the comprehensive assessment over time. This study aims to examine the associations between early life exposures in preterm infants and metabolic outcomes in adolescence, which represents an area of major translational importance.

## Background

The Developmental Origins of Health and Disease hypothesis suggest that nutritional imbalance during critical windows in early life can permanently influence long-term development and disease in later life [1]. Whilst the majority of epidemiological and other studies relate to infants born at term, there are increasing data, supported by controlled longitudinal studies, to show that similar effects occur in infants born preterm (<37 completed weeks gestation) [2]. Preterm births account for 5-10% of births in the UK and almost 10% of all births worldwide, representing more than 15 million births globally every year [3]. In developed countries, survival has dramatically improved in the last few years. More than 50% of babies born at 24 weeks gestation are now regularly surviving long term [4]. Despite these improvements, providing adequate nutrition to preterm infants is challenging and growth failure is common [5]. Most extremely preterm infants (<32 weeks gestation) require support with parenteral nutrition, metabolic ‘immaturity’ may limit nutrient intake, and enteral feeds take time to establish. Expressed breast milk is associated with a range of benefits in the short-term (e.g. reduction in the incidence of necrotising enterocolitis [6], a potentially fatal illness associated with milk feeds) and long-term (e.g. improved cognitive outcome), but alone will not meet nutrient requirements without fortification [7].

Because of these nutritional and other challenges, preterm infants accumulate nutrient deficits during hospital stay and most are discharged with weights below the 10^th^ centile. Many preterm infants demonstrate catch up in weight after hospital discharge, a time period equivalent to that in term born infants known to be strongly associated with later metabolic risk [8]. Children and adults born preterm demonstrate important differences in many aspects of their biology: cognitive outcome is worse [4], blood pressure is higher [9] and there is an increased prevalence of type II diabetes [10]. Other aspects remain less certain, for example data regarding the timing and progression of puberty after preterm birth are still conflicting [11,12]. Randomised controlled trials (RCTs) have shown that growth and nutrient intakes in early life in preterm infants affect metabolic outcomes in later childhood such as abnormal fat deposition, insulin sensitivity and vascular health [13-15]. Studies also show that early nutrition affects later cognitive outcome [16,17]. However, there are few longitudinal cohorts of preterm infants and there remain major uncertainties about how best to feed preterm infants. The risks and benefits of rapid growth promotion in both the pre- and post-discharge period, and in later childhood remain to be determined [18].

Along with accumulating evidence that early life exposures are key factors in determining later health, current lifestyle factors such as diet and physical exercise are also extremely important and provide an opportunity for targeted intervention. Recent efforts to improve nutritional status in adolescent children have proven difficult, and many of the factors that require change (e.g. diet, mealtimes, physical activity etc.) exist in a complex socio-cultural environment. In addition, although there is some evidence that short-term outcomes such as BMI (or fat mass index) can be modified, there are few data showing that insulin resistance or other markers of the metabolic syndrome are modifiable in children [19].

Determining the role of early life events in modulating the later risk of type 2 diabetes, obesity or hypertension require long term study as the underlying abnormal metabolic processes take decades before manifesting as disease. There are many challenges for longitudinal cohort studies, especially in high-risk cohorts such as children born preterm, including attritional losses over time [20] and changes in health care interventions that might limit generalizability to contemporary practice. Despite the enormous wealth of literature pertaining to animals, there are few prospective cohort studies in humans with detailed phenotypic characterization. Examples include the Avon Longitudinal Study of Parents and Children [21] and the Gateshead Millenium Study [22]. In some cohorts, follow up rates remain an issue, and most have only been tracked into childhood. Large-scale epidemiologic studies have provided a wealth of information on early growth patterns and long-term outcomes [23,24] but phenotypic characterisation of infant and childhood events are largely restricted to auxological parameters (i.e. weight, height and body mass index (BMI)) and there are few data with direct assessment of body composition. Whilst detailed phenotypic characterisation is present in certain longitudinal studies, most lack the granularity of information around delivery and in early postnatal life. Most regular birth cohorts also have preterm births under-represented, as difficult births are more likely to be omitted from sample collection due to other clinical priorities. Most adult cohorts are unable to determine relative differences in lean or fat mass accretion in early childhood, and data on early nutrient intake is largely limited to population estimates [25,26].

Much of the current data available from preterm infants is in cohorts recruited to studies in the 1980’s, an era pre-dating the widespread use of antenatal steroids and surfactant therapy. These two key perinatal practices have had dramatic effects on morbidity and mortality, and will have major effects on later outcomes. The Newcastle Preterm Birth Growth Study (Newcastle PTBGS) is a unique cohort of children born preterm in the late 1990’s. The major strengths are the detail of early nutritional and growth exposures, and the comprehensive assessment over time that includes growth, metabolic, neuro-cognitive, and body composition outcomes. The cohort also enables examination of outcomes from an RCT perspective, thereby avoiding some of the challenges of reverse causation and confounding.

Birthweight is a relatively crude measure of fat or lean mass, but despite this a clear relationship exists between birthweight and later lean mass and muscle strength [27,28]. This appears to be independent of muscle mass, suggesting that fetal and possibly infant growth permanently alter cellular function [29]. Intramyocellular and intrahepatic lipid accumulation alongside abdominal lipid depots compromise the ability to oxidise lipid, demonstrated by reduced muscle mitochondrial capacity and whole body cardiorespiratory fitness, both of which are key determinants of insulin sensitivity. Physical activity and inactivity are also important environmental modulators of insulin sensitivity through their direct and indirect influence on insulin action and also their role in weight maintenance. This strongly suggests that a comprehensive approach to outcome measurement in intervention trials is needed rather than focusing simply on weight loss or change in BMI. There are limited data on regional lipid deposition, oxidative capacity and glucose control across childhood, especially in those with detailed information of early growth and nutrient exposure.

To examine the relative importance of early growth and nutritional factors, and how these might confound or interact with later childhood factors requires study in cohorts with detailed phenotypic data. Genetic and/or epigenetic characterisation is likely to further improve understanding including possible mediating mechanisms (including molecular factors such as epigenetic processes) and establishing the direction of causality. In addition, there is a need to determine whether robust markers of later risk for type 2 diabetes, such as childhood insulin resistance (measured with fasting insulin and glucose and/or using an oral glucose tolerance test (OGTT), or intrahepatic/intramyocellular accumulation are modifiable. To do this, there is a need to first determine the current range of these parameters in high-risk groups and examine relationships with current measures of diet, physical activity and cardiorespiratory fitness, and establish the types of interventions that might be effective in decreasing the risk.

The aim of this study is to examine the associations between early life exposures in preterm infants and later metabolic outcomes and their mediators. We will follow up a cohort of preterm infants from the Newcastle PTBGS as teenagers to determine the presence of novel metabolic biomarkers and correlate these with lifestyle factors.

## Methods

### Study setting

The current study is embedded within the Newcastle PTBGS, which is a prospective cohort study based on two RCTs of varying nutrient intake in preterm infants: one study where the intervention was in the post-discharge period (standard versus nutrient enriched formula), and the second spanning the pre- and post-discharge period where differing protein, but iso-caloric formula intake densities, were fed [30,31]. All participants were born and recruited between 1993 and 1998 from a single tertiary neonatal centre, the Special Care Baby Unit at the Royal Victoria Infirmary in Newcastle upon Tyne. A control group of infants who were primarily breast-fed on hospital discharge, and some co-twins supplemented the two interventional cohorts. The infants of both RCTs and controls were combined to form the Newcastle PTBGS cohort.

The RCTs aimed to recruit infants who were born ≤34 weeks gestation and had a birthweight of ≤1750 g. In the first RCT, referred to as the ‘growth study’ , infants were randomised to one of two formulae on discharge from hospital. They were either fed (A) a preterm infant formula from discharge to 6 months post-term, (B) a standard term formula from discharge to 6 months or (C) the preterm formula from discharge to term and then the standard term formula until 6 months (‘crossover’ group). Preterm formula had an energy density of 80 kcal and 2.2 g protein, and term formula was 67 kcal and 1.6 g protein per 100 mL [32]. Further details of the nutrient composition of the formula are provided elsewhere [32]. A control group of breastfed babies was also included. Infants were seen at the outpatient clinic fortnightly between discharge and term and monthly between term and 6 months corrected age. At each clinic visit, milk intake, auxology (length, weight, mid-arm circumference, MAC, occipito-frontal head circumference, OFC) and serum biochemistries were determined. Formula milk intake was determined by providing pre-weighed ready to feed formula, and re-weighing used bottles. Body composition was assessed at different time points including hospital discharge, term, 12 weeks, 6 months, and 12 months using dual energy x-ray absorptiometry (DXA) scans. Auxological measures were repeated at 18 and 24 months. Bayley Scales of Infant Development (BSID) mental development index (MDI) and psychomotor development index (PDI) tests were assessed at 18 months [30].

In the second RCT, the ‘protein study’ , 77 infants were randomised to one of three preterm formulas that were iso-caloric (80 kcal/100 mL), but differed in protein density (A - 3.3 g, B - 3.0 g, and C - 2.7 g per 100 kcal) [31]. Infants were recruited once full enteral feeding had been successfully established and they continued on the trial formula post-discharge until 12 weeks post-term. Milk intake, auxology and serum biochemistries were determined weekly during inpatient stay, and every 4 weeks until 12 weeks. Auxology was repeated 6 monthly until 24 months. Body composition was assessed using DXA at discharge and at 12 weeks.

In both studies, a social questionnaire addressing aspects of family structure, parental employment, education history, smoking etc., was completed prior to hospital discharge. Although the inclusion criteria for randomisation into the two RCTs was a gestational age of ≤34 weeks, 1 set of low birthweight triplets of 36 weeks gestation were included as breastfeeding controls, along with siblings of eligible infants whose birthweight was >1750 g. Because of a small time overlap in the recruitment period for the two RCTs (randomised infants could only join one RCT) there were 4 breast fed control infants who were initially included in study reports for both studies, but thereafter are only included once in the combined cohort. Mean gestation for the cohort (n = 247) was 30.9 weeks (range 24.7-36.4 weeks) and birthweight 1392 g (range 690-2200 g). One hundred and twenty five were male. There were no significant differences in gestation or weight between boys and girls.

The Newcastle PTBGS has previously been followed up on three occasions since the initial randomised controlled trials (see Table 1). The current study, GROWMORE, will be phase four of follow-up [33].

**Table 1 T1:** Data collected during follow-up phases of the Newcastle preterm birth growth study

**Phase 1- Growth and Protein study RCTs**	**Phase 2- Cognitive/Behavioural follow-up at 10 years**	**Phase 3- Early adolescent follow-up**	**Phase 4- Late adolescent follow-up**
**(n = 247)**	**(n = 92 from 113 in growth study)**	**(n = 153 from 247 in RCTs)**	**(n = 60 from 153 in phase 3)**
**Auxology:**		**Auxology:**	**Auxology:**
Length*, weight, OFC at birth, discharge, term, 1,2,3,6,12,18,24 months corrected age	Wechsler Intelligence Scale for Children version 3 (WISC III) including Wechsler Objective Numerical Dimensions (WOND), Wechsler Objective Reading Dimensions (WORD) and Wechsler Objective Language Dimensions (WOLD). Achenbach Child Behaviour Checklist. Vineland adaptive behavior scales (n = 113)	Height, weight, OFC, abdominal circumference, waist/hip ratio	Height, weight, waist circumference, blood pressure. Self assessment of pubertal status
		Blood pressure	
		Self-assessment of pubertal status	
		(n = 153)	
**Bloods:**		**Bloods:**	**Bloods:**
Serum Biochemistry weekly till term then 1,2,3 months		Short oral glucose tolerance test	2 hour glucose tolerance test, 25-OHD, lipid profile, liver function, sex hormones, RNA, cellular DNA and serum to store
		Fasting Lipids: cholesterol, triglycerides	
Leptin, adiponectin, insulin and IGF1 (n = 70 subset)		Leptin, adiponectin	
		(n = 109)	
**Body composition:**		**Body composition:**	**Body composition:**
DXA at discharge and/or term, 3,6,12 months (6 and 12 months only growth study)		DXA scan and bio-impedance	BODPOD
		(n = 139)	IHL and IMCL deposition using ^1^H magnetic resonance spectroscopy
Social questionnaire	Socioeconomic deprivation score	Social and family history	SCRAN-24 dietary information
			Actigraph data
			Intervention and feedback questionnaires
BSID II MDI and PDI at 18 m (Growth study n = 113)			

*Length not available pre-discharge for most.

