#### Power calculation

Determining an appropriate sample size for this study is difficult given there are multiple outcome variables, including some exploratory, being investigated. Using results from phase three of this study, we know that insulin sensitivity is strongly associated with fat mass index. Using the effect size from our data of r^2^ = 0.12, with 80% power at the 5% level of significance we estimated that we would need ~60 patients to be able to detect a significant difference. Previous work looking at mitochondrial oxidative function in the Magnetic Resonance centre required a sample size of only 10 patients to determine a 10% reduction in τ_1/2_ PCr [34]. Therefore we have chosen to study 60 young people, as this will ensure an adequate sample size for two of the main outcome variables.

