#### Current study population and recruitment

All children who participated in phase 3 (n = 153) will be approached, via mail, after verifying postal address through their general practitioner. We will approach the young people sequentially starting with the oldest, but no other active selection process will be used. A recruitment letter, explaining the study and assessments in detail will be sent to all parents whose children fit the above criteria and a simplified patient information sheet sent to the young person. Informed, written consent will be obtained from parents and where appropriate, participants, before participation.

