#### Statistical analysis

Data will be analysed using Stata (v11, StatCorp LP, Texas, USA). Mann–Whitney U or t tests will be used to demonstrate that the follow-up sample is broadly representative of the original cohort for key variables such as gestation and birth weight. Correlation analysis will be used to examine the relationships between the different measures of body composition and the MR measures of lipid deposition and to examine the interaction between vitamin D and oxidative capacity by ^31^P MRS and cardiorespiratory fitness. To assess associations between infant and childhood growth and subsequent metabolic outcomes, we will develop separate linear regression analysis models using insulin sensitivity and body composition (fat mass index and lean mass index) as the dependent variables. Half-time of PCr recovery (τ_1/2_ PCr) will be used as dependent variable for regression models examining muscle mitochondrial function in relation to insulin sensitivity, directly measured exercise, body composition and vitamin D levels (as independent variables). In all multiple linear regression models adjustment will be made for potential confounding factors such as sex, gestation, age at follow-up, birthweight z-score, infant growth velocity, post discharge feeding pubertal status and whether mechanical ventilation was required in the neonatal period (which we used as a proxy for illness severity). Bland Altman analysis will be used to assess agreement between the different techniques used to assess body composition.

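### Co-twins, siblings and a triplet set can enter the sample of 60, but the named tests, correlations and regressions make no allowance for relatedness, so standard errors may be modestly misstated

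*Protocol article*

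**What the plan says.** **Who is in the cohort.** The Study setting section explains how the two randomised cohorts were enlarged: "A control group of infants who were primarily breast-fed on hospital discharge, and some co-twins supplemented the two interventional cohorts". It adds that "1 set of low birthweight triplets of 36 weeks gestation were included as breastfeeding controls". Brothers and sisters above the trials' weight limit were taken in as well. It gives no count of twins or siblings in the 247 originally recruited, the 153 seen in phase 3, or the 60 now planned.

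**Who is invited.** All 153 phase 3 participants are to be contacted. On the order, the recruitment section says: "We will approach the young people sequentially starting with the oldest, but no other active selection process will be used". Nothing limits a family to one participant.

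**How many.** The Power calculation section starts from "Using the effect size from our data of r^2^ = 0.12" for insulin sensitivity against fat mass index, with 80% power at the 5% level, and arrives at about 60. It concludes: "Therefore we have chosen to study 60 young people, as this will ensure an adequate sample size for two of the main outcome variables".

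**How the data are analysed.** The Statistical analysis section plans t or Mann–Whitney tests to check that the sample is representative, and correlations among body composition, lipid, vitamin D and oxidative measures. For the growth questions it says "we will develop separate linear regression analysis models using insulin sensitivity and body composition". A further regression takes the half-time of phosphocreatine recovery as the outcome. The listed adjustment factors are given as examples. None identifies the family, and no clustered error or random effect is mentioned.

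**The concern.** Children of the same pregnancy share gestation, birth date and half or more of their genes, and usually a household with its diet and habits. Their body fat, insulin sensitivity and liver fat are likely to be correlated after adjustment for the listed covariates. The named methods, in their usual form, count each child as an independent observation.

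The recruitment order makes complete sets more likely. Co-multiples share a birth date, so they sit next to each other in an oldest-first list.

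The study's main aim is to relate early-life exposures to metabolic outcomes. Some of those exposures (gestation, age at follow-up, possibly feeding after discharge) are wholly or largely common to a pair. For these, a second twin adds less information than an unrelated child, and unadjusted intervals are too narrow. For exposures that differ within a pair, such as birthweight z-score or growth velocity, the error can go the other way. With 60 participants and power set close to 80%, there is little slack.

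**Working it through.** **Inputs from the article.** Planned n = 60; r² = 0.12; power 80%; 5% level, taken as two-sided because the article does not say.

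**Assumed inputs.** The number of complete pairs among the 60 is taken as 6 to 12, so the share of children with a co-multiple in the sample is f = 12/60 = 0.2 to 24/60 = 0.4. The within-pair correlation of the outcome is ICC_y = 0.3 to 0.7. The within-pair correlation of the exposure is ICC_x = 1 if fully shared and 0.5 as an example for an individually measured exposure. None of these is in the documents. The triplet set was not modelled separately.

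**Step 1: reproduce the stated sample size.** For one predictor, f² = 0.12/(1 − 0.12) = 0.1364. The noncentral F test with noncentrality f² × N first reaches 80% power at N = 60 (80.3%). The article's figure of about 60 is therefore reproduced, as a test on 60 independent persons. The Fisher z approximation would give 64, with 77.9% power at 60.

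**Step 2: variance inflation.** For a slope or correlation with pairs,

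DE = 1 + f × ICC_y × ICC_x.

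Effective n = 60/DE. The true standard error is √DE times the reported one. The actual type I error at nominal 5% is 2 × [1 − Φ(1.96/√DE)].

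**Step 3: results.**

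| Case | DE | √DE | Effective n | Type I error |
|---|---|---|---|---|
| Shared exposure, 6 pairs, ICC_y 0.3 | 1 + 0.2 × 0.3 × 1 = 1.06 | 1.030 | 56.6 | 5.7% |
| Shared exposure, 12 pairs, ICC_y 0.7 | 1 + 0.4 × 0.7 × 1 = 1.28 | 1.131 | 46.9 | 8.3% |
| Individual exposure, 6 pairs, both ICCs 0.5 | 1 + 0.2 × 0.5 × 0.5 = 1.05 | 1.025 | 57.1 | 5.6% |
| Individual exposure, 12 pairs, both ICCs 0.5 | 1 + 0.4 × 0.5 × 0.5 = 1.10 | 1.049 | 54.5 | 6.2% |

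**Step 4: power for the association in the power calculation.** Fat mass index is measured on each child, so an individual-exposure row applies. At an effective n of 57.1 the F test has 78.3% power, against 80.3% at 60. Restoring it would need 60 × 1.05 = 63 children.

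**Step 5: check by simulation** (40,000 runs, n = 60, standard correlation test). Type I error was 5.1% with no pairs, 5.6% with 6 pairs and both ICCs 0.5, 6.0% with 12 pairs and both ICCs 0.5, and 8.4% with 12 pairs, ICC_y 0.7 and a fully shared exposure. These agree closely with the formula.

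**Step 6: direction.** The added term has the sign of ICC_x. If the exposure is unrelated within pairs, DE = 1 and nothing is lost. If it tends to diverge within pairs, which can happen once shared factors such as gestation are adjusted for, DE falls below 1 and the unadjusted standard error is too large.

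**The case against.** The strongest reply is that the article does not state an independence assumption. It names linear regression without a variance estimator. Clustered errors are still linear regression, so they would add to the text and not contradict it, and a condensed article may leave that choice to an analysis plan that is not shown. A reader might infer that the article commits to ordinary least squares with independent errors; it does not say so. This weakens the point for the regressions more than for the t tests and correlations, which in standard form have no place for a family term. What remains is that the article itself reports the related children, names its tests, outcomes and example covariates, sets the sample size on independent persons, and connects none of these to relatedness. The open covariate list does not settle it, since one more confounder does not remove residual correlation within families.

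Second, the numbers may be small. The siblings above 1750 g may be the same children as the co-twins, and only 60 of 153 are studied, so the triplets or any given pair may not enter. That stands, and it is why no single figure can be given.

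Third, most planned exposures (activity, vitamin D, body fat, liver fat) are measured on each child, and there the distortion is slight. That also stands. A reader might apply the inflation for a fully shared exposure to the power calculation and report a large loss: an effective n of 46.9 would give 69.6%. The documents do not support this, because fat mass index is not common to a family.

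**Conclusion.** The point holds in a limited form. Related children are in the sampling frame, both members of a pair can enter, and the named analyses do not account for it. Standard errors and p-values may therefore be misstated, in a direction that depends on the exposure.

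For individually measured exposures the likely type I error is about 5% to 6%. It reaches about 8% only with many pairs, high outcome correlation and a fully shared exposure. All of this rests on the assumed pair counts and correlations.

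Two stronger conclusions might be drawn and are not supported. One is that the reported p-values will certainly be wrong, which cannot be said while the number of related children among the 60 is unknown. The other is that the sample size of about 60 is an arithmetic error; it is reproduced exactly for independent persons.

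The correction is worth making because it is standard and cheap, not because the expected damage is large.

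**What to change.** Add the following to the Statistical analysis section:

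- Report how many of the 60 have a co-multiple or sibling in the sample, and how many families there are.
- Fit all regressions with standard errors clustered on family, with a small-sample correction, or with a random family intercept. With 6 to 12 pairs there would be 60 − 6 = 54 to 60 − 12 = 48 families. A random-intercept variance would be estimated from the few multi-child families only, so clustered errors may be the steadier choice.
- Take each correlation as the standardised slope from the same clustered model. The comparison with the original cohort can likewise be run as a clustered regression on a group indicator.
- Add a sensitivity analysis with one randomly chosen child per family. It would use 48 to 54 children under the same assumption, so it is a check and not a replacement.

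**Cost.** A sentence or two of text, a little more analysis work, and slightly wider intervals for shared exposures. Recruitment and measurements do not change. The article does not say that a family identifier is held; it is assumed to be derivable from birth records and the family-structure questionnaire, and this should be confirmed.

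### Two largely sequential feeding trials are pooled, but trial of origin is not a named adjuster; this matters most for nutrient-intake exposures

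*Protocol article*

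**What the plan says.** Under Study setting, the article describes two randomised trials and then says "The infants of both RCTs and controls were combined to form the Newcastle PTBGS cohort". In the growth study, one arm received "a preterm infant formula from discharge to 6 months post-term"; randomised feeding began at discharge in every arm. In the protein study, infants entered in hospital once fully enterally fed, and "they continued on the trial formula post-discharge until 12 weeks post-term". The trials were recruited at mostly different times: four breast-fed controls were reported in both, "Because of a small time overlap in the recruitment period for the two RCTs". 

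The DXA schedules also differ. The growth study scanned at "hospital discharge, term, 12 weeks, 6 months, and 12 months using dual energy x-ray absorptiometry (DXA) scans". For the protein study, "Body composition was assessed using DXA at discharge and at 12 weeks". Table 1 says the same: "DXA at discharge and/or term, 3,6,12 months (6 and 12 months only growth study".

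The Statistical analysis section plans separate regressions of insulin sensitivity and body composition on infant and childhood growth. In all multiple regressions, "adjustment will be made for potential confounding factors such as sex, gestation, age at follow-up, birthweight z-score, infant growth velocity". The list goes on to post-discharge feeding, pubertal status and neonatal ventilation. Trial of origin is not named, and no within-trial analysis is described.

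**The concern.** Trial of origin is part of the design. It fixes the feed and its timing, and it tracks birth era. Randomisation protects comparisons between feeds within each trial; a comparison between trials is observational. The Background presents the cohort's trial origin as a protection against confounding, and the Discussion says the timing of dietary intervention may be critical. Timing is one of the things that differs between the trials.

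Hypothesis 4 relates adolescent outcomes to infant growth, body composition and nutritional intake. If trial is related to one of these exposures and also to the outcome, leaving it out puts the between-trial contrast into the slope. Differences in the same direction can create an association; differences in opposite directions can hide one.

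Two named covariates overlap with trial, but neither is sure to capture it. Post-discharge feeding has no stated coding; a coding by formula type would put the growth study's preterm-formula arm with all three protein-study arms. Age at follow-up depends on visit date as well as birth date. Under Current study population and recruitment, the oldest are invited first, so younger participants are seen later and the link between age and birth era loosens.

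**Working it through.** **The plan's own sample size.** Inputs from Power calculation: r² = 0.12, 80% power, 5% level (two-sided assumed). F test for one slope: f² = 0.12/0.88 = 0.136, noncentrality 60 × 0.136 = 8.18, power 80.3% at n = 60. The stated figure of about 60 is reproduced and is not in dispute. It corresponds to r = √0.12 = 0.35.

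**How large a spurious correlation could be.** With no within-trial association, share p from one trial, and a difference of d within-trial SDs in both exposure and outcome:

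r = p(1−p)d² / [1 + p(1−p)d²]

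At p = 0.5: d = 0.5 gives 0.0625/1.0625 = 0.06, and d = 0.8 gives 0.16/1.16 = 0.14. At p = 0.3 the values are 0.05 and 0.12. If either difference is zero, r is zero.

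**How far protein density separates the trials.** Study setting gives the figures. Growth study: preterm formula 2.2 g per 80 kcal = 2.75 g/100 kcal; term formula 1.6 g per 67 kcal = 2.39. Protein study: 2.7, 3.0 and 3.3. Assume equal arms, and put the crossover arm midway at 2.57. The means are then 2.57 and 3.00, and the SDs 0.148 and 0.245. The pooled SD is √[(0.148² + 0.245²)/2] = 0.202, so the gap is 0.431/0.202 = 2.1 within-trial SDs.

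**False-positive rates.** Simulation with n = 60, equal split, no within-trial association, 20,000 runs per cell. Assumptions:
- Births are even over five years, with about half a year of overlap between the trials.
- Age at follow-up keeps either all or only one fifth of the birth-date spread, plus a random 0.25-year SD.
- The protein-density rows cover formula-fed infants only.
- Post-discharge feeding is left out, because its coding is not given.

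| Exposure; between-trial difference | No covariates | Age, full spread | Age, one fifth of spread | With trial term |
|---|---|---|---|---|
| General; 0.3 SD in both | 5% | 5% | 5% | 5% |
| General; 0.5 SD in both | 7.5% | 5% | 6% | 5% |
| General; 0.8 SD in both | 18% | 7% | 10.5% | 5% |
| Protein density; outcome 0.3 SD | 13% | 7% | 9% | 5% |
| Protein density; outcome 0.5 SD | 27% | 9% | 16% | 5% |

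The plan adjusts for age, so the two age columns are the relevant ones. A 70:30 split gives similar age-adjusted rates: about 8–10% for the general exposure at 0.8 SD, and about 11–16% for protein density at 0.5 SD.

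**Cost of the term.** Holding partial r² at 0.12 with n = 60, power is 80.10% with the exposure and the eight named adjusters, and 80.07% with trial added. If the exposure differs by trial, the variance of its slope rises by 1 + p(1−p)d². That is 1.05–1.16 for d = 0.5–0.8 (p = 0.3–0.5), and 1 + 0.25 × 2.13² = 2.1 for protein density. For the age coefficient, take each trial to span 2.75 years with means 2.25 years apart. The within-trial variance is 2.75²/12 = 0.630 and the between-trial variance 0.25 × 2.25² = 1.266. The inflation is 1 + 1.266/0.630 = 3.0, a standard error about 73% larger.

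**The case against.** The strongest reply is that the adjustment list is open-ended and stands in a condensed article, so it does not show that trial will be left out. That is correct: the point is that trial is not named, not that it is excluded. Naming it still matters, because an open list commits the analyst to nothing on a design factor, while a narrower item such as ventilation is written in.

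Second, the named covariates already do much of the work. This also stands in large part. Age adjustment alone brings the 18% in the table down to about 7%. If post-discharge feeding were coded by randomised arm, it would identify the trial for every randomised formula-fed infant. The article does not say that it is.

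Third, a reader might infer that every early-life association is contaminated. The documents do not support that. Confounding needs trial to be related to both exposure and outcome after adjustment, and no such differences are reported. Both trials come from one centre with the same gestation and birthweight targets. With oldest-first recruitment the 60 may come mostly from one trial, which would shrink the problem: at a 90:10 split the unadjusted rate at 0.8 SD is only about 7%.

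Fourth, a reader might take the DXA schedules as further mixing. They are not. A model using 6- or 12-month DXA can contain only growth-study infants, and Table 1 says so. What is needed there is a label.

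**Conclusion.** The point holds in a limited form. The text documents the pooling, the largely sequential recruitment and the differing feeds; trial of origin is not among the named adjusters, and the two proxies capture it only partly. For general growth exposures the likely effect is small: about 5–7% false positives after age adjustment for assumed differences of 0.5–0.8 SD, rising to about 11% only if age retains little of birth era. For nutrient intake under hypothesis 4, the difference in formula composition is documented and only the outcome difference (0.3–0.5 SD) is assumed; the rate is about 7–16%. That range treats formula density as the exposure. Measured intake could separate the trials less or more; the Discussion notes that term-formula infants took larger volumes. The 18% and 27% figures come from models without covariates and should not be read as the plan's error rates.

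**What to change.** In the Statistical analysis section, name trial of origin (growth or protein study) as a covariate in the regressions of adolescent outcomes on infant growth, body composition or nutritional intake. Assign breast-fed controls and co-twins to the study that recruited them, and fix a rule in advance for the four controls reported in both. In pooled models, take infant body composition from the DXA times that both trials share (discharge and 12 weeks). Label any model using 6- or 12-month DXA as growth study only.

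The cost is a sentence or two and one degree of freedom, using study membership that should already be on file. Power stays at about 80.1% with partial r² held at 0.12. Two losses should be accepted openly. If trial and age are nearly collinear, the age coefficient becomes clearly less precise. For exposures that differ strongly by trial, such as protein density, the interval widens (slope variance roughly doubled), because the precision given up came from the between-trial contrast.
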